## Abstract

**Background:**

Insomnia (difficulty falling or staying asleep) is a common issue among breast cancer survivors, significantly impacting their quality of life. Current treatments, primarily pharmacological and psychological, have limitations: the former often causes side effects, while the latter faces accessibility barriers. Long-snake moxibustion (LSM), a traditional Chinese medicine (TCM) technique, involves applying moxibustion along the governor vessel, which is an important meridian in TCM that plays a key role in regulating brain function. LSM is characterized by its minimal side effects, ease of application, and cost-effectiveness, with preliminary studies supporting its potential for treating insomnia. This study aims to further investigate the therapeutic effectiveness of LSM in alleviating insomnia among breast cancer survivors and to explore its underlying mechanisms.

**Methods:**

This single-center, rater-masked, randomized controlled trial will enroll 100 breast cancer survivors with chronic insomnia, who will be randomly assigned in a 1:1 ratio to either the LSM group or a waitlist control group. During the 4-week treatment period, all participants will receive standard care, with the LSM group additionally receiving LSM treatment twice a week. The primary efficacy outcome is the change in Insomnia Severity Index (ISI) score at the end of the intervention. Secondary outcomes include changes in hypnotic medication use, Pittsburgh Sleep Quality Index (PSQI) scores, Piper Fatigue Scale (PFS) scores, and Functional Assessment of Cancer Therapy-Breast (FACT-B) scores. Mechanistic evaluations will assess serum biochemical markers, gut microbiota composition, and metabolomic profiles.

**Discussion:**

If proven effective, this trial will provide critical clinical evidence supporting LSM as a viable and accessible treatment for insomnia among breast cancer survivors. The findings could influence clinical practice by offering a non-pharmacological treatment option, improving patient outcomes, and reducing dependence on pharmacological interventions. Furthermore, exploring the underlying mechanisms may enhance our understanding of how LSM works, paving the way for future research.

**Clinical trial registration:**

http://itmctr.ccebtcm.org.cn/, identifier ITMCTR2024000578.

## Introduction

1

Breast cancer represents a significant global health challenge for women, standing as the most commonly diagnosed malignancy and the leading cause of cancer-related mortality. Epidemiological data from 2020 revealed approximately 2.3 million new cases of breast cancer and 685,000 related deaths worldwide, highlighting the substantial burden of this disease (1). As a complex and heterogeneous condition, breast cancer manifests through various molecular subtypes, with hormone receptor-positive (HR+) breast cancer constituting the predominant molecular subtype, representing nearly 70% of all breast cancer cases (2). The pathogenesis of HR + breast cancer is intrinsically linked to estrogen signaling pathways, necessitating prolonged endocrine therapy typically spanning 5–10 years as a fundamental component of adjuvant treatment to reduce recurrence risk (3).

Among the spectrum of cancer survivorship issues, insomnia emerges as a particularly prevalent and clinically significant comorbidity, characterized by persistent difficulties in sleep initiation, maintenance, or non-restorative sleep despite adequate opportunity for sleep (4). This sleep disorder is strongly associated with multidimensional health consequences, including increased fatigue, cognitive impairment, immune dysregulation, and elevated risk of psychiatric comorbidities such as depression and anxiety disorders (5, 6). The critical role of sleep in maintaining physiological homeostasis is well-established, with studies suggesting that around 7 h of sleep per night is optima (7). Notably, among cancer survivors, the prevalence of insomnia is significantly higher in breast cancer patients, reaching approximately 62% (8), a phenomenon potentially mediated through neuroendocrine dysregulation secondary to endocrine therapeutic interventions (9).

Current therapeutic approaches for insomnia predominantly include pharmacological and psychological interventions (10). Pharmacological treatments often encompass benzodiazepines, non-benzodiazepine agents, barbiturates, and other sedatives (11). While these interventions demonstrate considerable short-term efficacy, their long-term application is generally discouraged due to potential risks of tolerance, dependency, and adverse side effects (12). Psychological interventions, particularly cognitive-behavioral therapy (CBT), have shown effectiveness in improving sleep quality among breast cancer patients (13). However, the substantial labor demands and elevated costs associated with CBT limit its accessibility (14), underscoring the necessity for alternative therapeutic strategies.

Moxibustion, a core component of traditional Chinese medicine (TCM), involves stimulating specific acupoints to treat various conditions and is recognized for its minimal side effects, operational simplicity, and cost-effectiveness. A systematic review has suggested that moxibustion may be effective in managing insomnia (15). Long-snake moxibustion (LSM), a specialized form of moxibustion applied along the governor vessel from GV14 (Dazhui) to DU2 (Yaoyu), is theorized in TCM to be associated with the brain and closely related to sleep regulation. Compared to conventional moxibustion, LSM offers broader acupoint stimulation with enhanced heat radiation and deeper tissue penetration (16). Additionally, existing studies have indicated the anti-tumor effects of moxibustion (17). Based on these considerations, we hypothesize that LSM could serve as a viable strategy for managing cancer-related insomnia.

To empirically investigate this hypothesis, we have developed a randomized controlled trial targeting breast cancer survivors, a population particularly susceptible to insomnia. This study will rigorously evaluate both the clinical efficacy and underlying mechanisms of LSM by analyzing changes in the Insomnia Severity Index (ISI), as well as examining serum biochemical markers, gut microbiota composition, and metabolomic profiles.

## Methods

2

### Study design

2.1

This study is designed as a single-center, rater-masked, parallel-arm, randomized controlled trial. We will recruit 100 breast cancer survivors diagnosed with insomnia from the Hospital of Chengdu University of Traditional Chinese Medicine. Participants will be randomly allocated in a 1:1 ratio to either the LSM intervention group or the waitlist control (WC) group. The study will span 9 weeks, comprising a 1-week baseline assessment phase, a 4-week intervention phase, and a 4-week post-treatment follow-up phase. Throughout the 4-week treatment period, both groups will receive standard care, with the LSM group additionally undergoing LSM therapy twice per week. This trial has been rigorously designed according to the Consolidated Standards of Reporting Trials (CONSORT) guidelines and will be reported following the 2013 Standard Protocol Items: Recommendations for Interventional Trials (SPIRIT) Checklist (see Supplementary material S1). The study flow is depicted in Figure 1.

**Figure 1 fig1:**
[figure not shown]
The flow diagram of this study. FACT-B, Functional Assessment of Cancer Therapy-Breast; ISI, Insomnia Severity Index; LSM, long-snake moxibustion; PFS, Piper Fatigue Scale; PSQI, Pittsburgh Sleep Quality Index; WC, waitlist control.

### Participants

2.2

#### Recruitment

2.2.1

A comprehensive, multi-channel recruitment strategy will be implemented to enroll participants, utilizing posters, media advertisements, and clinical referrals. Prospective participants will undergo an initial screening through face-to-face interviews and baseline assessments conducted by the research team to confirm their eligibility for the study. In line with ethical standards, detailed information regarding the study’s objectives, intervention procedures, potential benefits, and associated risks will be provided to ensure participants give fully informed consent before enrollment.

#### Inclusion criteria

2.2.2

Age range of 18 to 75 years.Female patients with a pathological diagnosis of breast cancer, stages I to III, according to the American Joint Committee on Cancer (AJCC) 8th edition staging system.Completion of primary breast cancer treatment (e.g., surgery, radiotherapy, chemotherapy, targeted therapy, or immunotherapy) for a minimum of 3 months, with the exception of ongoing endocrine therapy, which is permissible if administered for over 3 weeks.No signs of cancer recurrence or new primary tumor development.Diagnosis of chronic insomnia as defined by the Diagnostic and Statistical Manual of Mental Disorders, 5th edition (DSM-5) (18), according to criteria set by the American Psychiatric Association.Insomnia severity ranging from mild to severe, represented by an ISI score of 8 or higher.

#### Exclusion criteria

2.2.3

Diagnosis of other sleep disorders, such as sleep apnea, parasomnia, or narcolepsy.Engagement in shift work or having irregular sleep-wake patterns.Abnormal liver, kidney, or coagulation function tests, or the presence of serious diseases that may compromise the safety of the trial, including but not limited to respiratory disorders (e.g., severe asthma), cardiovascular diseases (e.g., coronary artery disease), and hematologic disorders (e.g., leukemia).Pregnant or breastfeeding women.

### Interventions

2.3

All enrolled participants will receive standardized care, comprising sleep hygiene education and, where applicable, hypnotic medication interventions. The sleep hygiene education will emphasize adherence to a consistent sleep schedule, optimizing the sleep environment, and avoiding the consumption of alcohol, nicotine, and caffeine for at least several hours before bedtime. Additionally, participants will be encouraged to engage in 180–300 min of low-to-moderate intensity physical activity per week, while avoiding exercise within 3 h of their intended sleep time. Emotional self-regulation strategies will be incorporated to further support sleep hygiene practices. Hypnotic medications, which are optional and not required for all patients, will be prescribed based on individual therapeutic needs and clinical assessments. These medications may include psychotropic drugs such as benzodiazepines, non-benzodiazepine agents, and narcotics. The type, dosage, and frequency of all prescribed medications will be meticulously documented to ensure comprehensive data collection.

In addition to the aforementioned standard care, participants in the LSM group will receive supplemental LSM therapy, administered twice weekly for a total of eight sessions. The LSM procedure will be conducted following standardized protocols established in previous clinical studies (19). The treatment area will extend along the spine from GV14 (Dazhui), located at the lower border of the spinous process of the seventh cervical vertebra, to DU2 (Yaoshu), located at the lower border of the spinous process of the second sacral vertebra, with a 3 cm extension on both sides of the spine. The acupuncture points within this 3 cm range include the 13 governor vessel points as well as 24 bladder meridian points. Detailed information on the specific acupuncture points is provided in Supplementary material S2. The LSM procedure will commence with the patient lying in a prone position, with the back fully exposed, followed by thorough disinfection of the targeted area. A 12 cm-wide, 70 cm-long piece of mulberry bark paper will then be placed along the spine’s midline, after which a trapezoidal ginger paste (base width: 6 cm, top width: 5 cm, height: 3 cm) will be evenly mounded from GV14 to DU2. A cylindrical moxa cone (5 cm in diameter and 3 cm in height) will subsequently be positioned on the ginger paste, aligned along its full length. The moxa cone will be ignited and allowed to burn completely before being replaced once more, ensuring sufficient heat stimulation across the treatment area. Each LSM session is estimated to last approximately 1.5 h.

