#### Primary efficacy outcome

2.4.1

The primary efficacy outcome will be the change in ISI score from baseline to the end of the 4-week treatment period. The ISI is a validated 7-item self-report measure that has demonstrated strong internal consistency and construct validity for evaluating insomnia severity in cancer patients (20). ISI scores are categorized as follows: 0–7 (no clinically significant insomnia), 8–14 (mild insomnia), 15–21 (moderate insomnia), and 22–28 (severe insomnia) (21). ISI assessments will be conducted at baseline, as well as at weeks 2, 4, 6, and 8 following the start of treatment.

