#### Secondary efficacy outcomes

2.4.2

Changes in ISI scores from baseline at all additional assessment time points.Treatment response rate, defined as the percentage of participants achieving a reduction of ≥8 points in ISI score from baseline at each assessment (22).Changes in hypnotic medication usage. To maintain consistency in subsequent analyses and reporting, all hypnotic doses will be converted to standardized diazepam equivalent doses. For participants using hypnotic medications, the average dosage over the preceding 2 weeks will be recorded at baseline, as well as at weeks 2, 4, 6, and 8 after treatment initiation.Changes in Pittsburgh Sleep Quality Index (PSQI) scores. The PSQI is a widely used questionnaire to assess sleep quality over the past month, comprising seven components that evaluate specific sleep-related features (23). Scores range from 0 to 21, with 0–5 indicating good sleep quality, 6–10 suggesting moderate sleep quality, 11–15 reflecting poor sleep quality, and 16–21 indicating very poor sleep quality. Assessments will be conducted at baseline, as well as at weeks 4 and 8 post-treatment initiation.Changes in Piper Fatigue Scale (PFS) scores. The PFS is a validated tool widely used to assess fatigue in cancer populations (24), evaluating four dimensions: behavioral, affective, sensory, and cognitive. Scores range from 0 to 10, with 0–3 indicating mild fatigue, 4–6 indicating moderate fatigue, and 7–10 indicating severe fatigue. Assessments will be conducted at baseline and at weeks 4 and 8 post-treatment initiation.Quality of life, assessed using the Functional Assessment of Cancer Therapy-Breast (FACT-B) scale, which includes a general cancer subscale (27 items) and a breast cancer-specific subscale (9 items) (25). Higher scores on the FACT-B indicate better quality of life. Assessments will be conducted at baseline, and at weeks 4 and 8 post-treatment initiation.

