### Blinding

2.7

Given the distinct nature of LSM therapy, creating a placebo moxibustion is challenging. Consequently, this study will be conducted as an open-label trial, with both participants and acupuncturists aware of their treatment assignments. To mitigate potential bias, blinding will be maintained for outcome assessors, data managers, and statisticians. During assessments, outcome assessors will use CRFs containing participant names, while both participants and assessors will be instructed to avoid discussing treatment allocation. Once assessments are complete, independent administrative staff overseeing randomization will replace participant names with coded labels, and group assignments will be replaced with anonymized labels. The anonymized dataset will then be provided to data managers and statisticians for analysis. Since statisticians will only have access to the anonymized dataset, they will conduct the analysis without knowledge of treatment group assignments, ensuring unbiased interpretation of results. After data analysis is finalized, the identities associated with the codes will be disclosed to the research team for accurate interpretation of the results.

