For the primary efficacy outcome (the change in the ISI score from baseline to the end of the 4-week treatment period), subgroup analyses will be conducted based on hypnotic medication use (yes, no) and insomnia severity (mild, moderate, severe) to further explore potential variations in the treatment effects of LSM across different subgroups. Additionally, sensitivity analyses will be performed for the primary efficacy outcome. Specifically, if missing values or non-normally distributed data are present, multiple imputation methods will be used to assess the impact of missing data, and generalized estimating equations will be employed as a non-parametric alternative for non-normally distributed data. Pre-specified per-protocol analyses will also be conducted. The per-protocol set will include all participants who completed the intervention and follow-up according to the study protocol. The results of the primary analysis will be compared with those from these sensitivity analyses to assess robustness.

All statistical analyses will be carried out using SPSS (version 26.0) and R (version 4.3.1). Two-tailed significance testing will be applied, with a *p*-value threshold of ≤ 0.05 indicating statistical significance.

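### No planned analysis of the week-4 ISI addresses hypnotics started or changed after randomisation, so the trial cannot show how far its primary result depends on differential hypnotic use

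*Protocol article*

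**What the plan says.** Protocol article, section 2.3 (Interventions), makes hypnotics part of standard care in both arms: "All enrolled participants will receive standardized care, comprising sleep hygiene education and, where applicable, hypnotic medication interventions". The prescribing rule is individual: "Hypnotic medications, which are optional and not required for all patients, will be prescribed based on individual therapeutic needs and clinical assessments". Use is recorded: "The type, dosage, and frequency of all prescribed medications will be meticulously documented to ensure comprehensive data collection". Section 2.4.2 makes change in hypnotic use a secondary outcome, in diazepam equivalents: "the average dosage over the preceding 2 weeks will be recorded at baseline, as well as at weeks 2, 4, 6, and 8".

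The eligibility criteria (2.2.2 and 2.2.3) do not mention a stable hypnotic regimen. Section 2.1 describes a 1-week baseline assessment phase and then standard care through the 4-week treatment period, with no run-in on that care.

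On blinding, section 2.7 says "this study will be conducted as an open-label trial, with both participants and acupuncturists aware of their treatment assignments". It also says "blinding will be maintained for outcome assessors, data managers, and statisticians". Prescribers appear in neither list.

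The endpoint (2.4.1) is self-reported: "The primary efficacy outcome will be the change in ISI score from baseline to the end of the 4-week treatment period". The model in section 2.9 adjusts for the baseline value and has fixed effects for endocrine therapy, time, group and time by group, with participant as a random effect. The sensitivity analyses named there are multiple imputation, generalized estimating equations and a per-protocol analysis. Section 2.9 also plans that "subgroup analyses will be conducted based on hypnotic medication use (yes, no) and insomnia severity (mild, moderate, severe") for the primary outcome.

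**The concern.** A hypnotic acts directly on what the ISI measures. If one can be started, raised or lowered between randomisation and week 4, and participants know their allocation, use may come to differ between the arms. The two directions pull against each other. A waitlist participant given a new or larger dose may report a better ISI without LSM. An LSM participant who cuts down, which the secondary outcome looks for, may report a worse one. The opposite pattern would enlarge the apparent benefit.

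The article treats endocrine therapy with care: a minimum duration at entry, stratification and a model term. Hypnotic use gets none of these. A permitted dose change is not a departure from the protocol, so the per-protocol set does not deal with it either. The Discussion presents LSM as an alternative to drug treatment, so readers will want to know whether the ISI difference holds apart from changes in hypnotics. The planned analyses cannot tell them.

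**Working it through.** **1. What each planned analysis can say about hypnotic changes before week 4**

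- Primary mixed model (2.9): nothing. It has no hypnotic term, at baseline or later.
- Multiple imputation: deals with missing ISI values, not with values observed after a dose change.
- Generalized estimating equations: aimed at non-normality.
- Per-protocol set: defined by completing intervention and follow-up as planned, with no hypnotic criterion.
- Subgroup by hypnotic use: the time of measurement is not given. Use at baseline says nothing about later changes. Use during the trial would form subgroups after randomisation, possibly affected by treatment.
- Mixed model for hypnotic dose (secondary): shows whether average dose differs between arms, but does not link this to the ISI.

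**2. The plan's own figures (2.8)**

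- Pilot ISI decrease: LSM 6.82 (SD 4.06), waitlist 3.24 (SD 2.38). Difference = 6.82 − 3.24 = 3.58.
- Pooled SD = √((4.06² + 2.38²)/2) = 3.33, so d = 3.58/3.33 = 1.08, as stated.
- Unequal-variance t-test, two-sided alpha 0.05, power 0.90: 20 per group (power 0.909; 19 gives 0.893). With 10% dropout, 20/0.9 rounds up to 23. Two strata: 2 × 23 = 46, as stated. The sample size is not at fault.
- With 45 evaluable per group (50 less 10%), power for 3.58 points is 0.999.

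**3. Illustration of size, on assumed inputs**

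Let q be the difference between arms in the proportion who start or increase a hypnotic by week 4, and g the ISI gain from doing so. The between-arm difference shifts by q × g. The article gives neither q nor g.

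- Assume q = 0.10 to 0.30 and g = 3 to 5. The shift is 0.10 × 3 = 0.3 to 0.30 × 5 = 1.5 points, or 8% to 42% of 3.58.
- If the excess is in the waitlist arm, the difference falls to between 3.28 (d = 0.99) and 2.08 (d = 0.63). Power with 45 per group is above 0.99 and 0.83 respectively; with 50 per group, 2.08 points still has power 0.87.
- Wider: q = 0.1 to 0.4 and g = 2 to 6 give 0.2 to 2.4 points. At the far corner the difference is 1.18 and power 0.38.
- If the excess is in the LSM arm and LSM itself does nothing, q = 0.2 and g = 4 produce a 0.8-point difference, which reaches p < 0.05 about 20% of the time. Over the wider range the chance runs from 0.06 to 0.92.

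Subtracting from 3.58 treats the pilot difference as free of hypnotic effects. Section 2.8 does not say what care the pilot arms received, so part of the shift may already be in that figure.

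**The case against.** The strongest reply is that the primary comparison is sound as written. Both arms receive standard care including hypnotics, LSM is added to it, and the randomised comparison estimates the effect of that addition. Hypnotic changes brought about by allocation are part of the effect. This stands. A reader might infer that the primary result is biased or confounded by hypnotics; the article does not support that. The comparison answers a legitimate question, though the article does not say that this is the question intended.

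Other parts of the reply also stand. Dose is compared between arms, so differential use would be visible. A hypnotic-use subgroup of the primary outcome is planned, so hypnotics are not ignored; pairing it with insomnia severity makes baseline the natural reading. A reader might infer that prescribers know the allocation and that patients adjust hypnotics at will. The first is only inferred from the open-label design, and the text says prescribing follows clinical assessment. Nor do the illustrative figures show that a true effect would be masked: at the worst case of the narrower range, power is still 0.83.

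The argument that all this may be left to a fuller analysis plan stands only in part. The article itself lists the model's terms and names its sensitivity analyses, and none of them reaches hypnotic changes.

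**Conclusion.** The point holds in a limited form. Hypnotics may be started or changed in both arms of an open-label trial with a self-reported endpoint and no stable-regimen criterion, and no planned analysis of the week-4 ISI addresses those changes. The effect of adding LSM to standard care is validly estimated. How far it depends on differential hypnotic use is not.

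Size and direction cannot be known from the article. The 0.3 to 1.5 points (wider range 0.2 to 2.4) rest entirely on assumed values of q and g, and there is no shift at all if use changes alike in both arms. The stronger statement, that the primary result inevitably mixes LSM with hypnotic effects, is not supported. The cost is to interpretation, with power seriously affected only if both assumed inputs are large. It is worth correcting because the data are already collected and the remedy is analysis wording.

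**What to change.** Leave prescribing as it is and use the doses already recorded.

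1. Add baseline hypnotic use (yes/no) as a fixed effect in the section 2.9 ISI model. This serves precision and chance imbalance; it does not cure later changes.
2. State that the primary analysis targets the effect regardless of hypnotic changes. Pre-specify one supplementary week-4 ISI analysis in which ISI values after a hypnotic start, or after a dose change from baseline in either direction, are set to missing and handled by the mixed model or multiple imputation. Report it with the numbers of starts, increases and reductions by arm. A participant whose change precedes week 2 keeps no follow-up ISI, so the text should say how such cases enter.
3. In the section 2.9 subgroup, specify hypnotic use at baseline. This is a clarification.

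Any analysis that scores starters or increasers as not improved should be secondary to this one and leave observed worsening unchanged. It should carry a warning that it can favour LSM, because it also removes ordinary waitlist improvement: with a waitlist excess of 10 to 30 percentage points and the pilot waitlist mean, 0.10 × 3.24 = 0.3 to 0.30 × 3.24 = 1.0 points. It would also leave reductions unaddressed.

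Cost: no new data or visits. The downside is one more supplementary result, which rests on a missing-at-random assumption and may differ from the primary. The wording should be fixed before the allocation codes are disclosed.
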